
#### The Digital Health Program: Clinical Web Application

The web application targets health care providers and provides them with the necessary tools to enroll patients into the digital health program, as well as a tool for following up and communicating with patients. The web application features content about the profile of each patient and their preferences, such as the level of detail that they are interested in about their upcoming surgery, stress management preferences such as music and virtual places, information about their medical history and demographics to facilitate the personalization of the stress-relief content, as well as a dashboard for physicians to facilitate the visualization of patient-reported input over time, such as anxiety and pain levels.

This web application is mainly used to enable HCPs to manage, monitor, and follow patients enrolled in digital health programs. Whenever available, it connects to the electronic health record of the client to automatically retrieve useful information of the users (credentials) and patients enrolled (eg, demographics, medical history, clinical reports, and laboratory tests) as well as to provide relevant information about patients undergoing surgery such as their stress level. The web application includes the following modules.

#### Profiler for Personalization Module

The profiler module gathers relevant information from patients about (1) the level of information they would like to receive regarding their surgery (general, more detailed, and graphical); (2) how they would prefer to manage stress (music preferences, virtual places, etc); and (3) other relevant information to create personalized intervention (education level, age, medical condition, etc). The information stored is adapted to individual needs and preferences that the user can change or modify at any time. All necessary actions were taken to ensure equality of use and avoid age and gender discrimination. Data from the patient profile (type or surgery, preferences, specific requirements, etc) are combined with lifestyle monitored data and implicit and explicit feedback of patients and caregivers when using the mobile app to update patient information and tailor the best stress management coach strategy in accordance with physicians’ recommendations.

#### Communication Module

This module enables communication with the mobile app users. It is based on asynchronous chat that can be used to exchange messages with health providers and contact them in case of an emergency. In addition, predefined messages can be configured to be sent to users at specific time points of the patient journey (ie, the day before the surgery, remind clinical appointments, etc).

#### Lifestyle Monitoring Module

This module enables the longitudinal visualization of the biometric information gathered through the mobile app, including physical activity and other information helpful in understanding patient behavior along the patient journey and monitoring his or her progress between clinical visits.

#### Patient Tracking Module

The patient tracking module helps HCPs track patient location and elapsed times between specific steps of the patient journey from admission to hospital discharge. Patients are automatically tracked using BLE beacons strategically installed in the hospital entrance, admission, surgery ward, and presurgery room. From that point onward, HCPs manually update patient tracking, which also triggers notifications to the caregiver’s mobile app, helping them to monitor their relative along the surgical journey (Figure 4).

**Figure 4 figure4:**
[figure not shown]
A screenshot of the Digital Health Program web application.

#### Self-assessment Module

The self-assessment module facilitates visual monitoring of psychometric information through validated patient-reported outcome measures and questionnaires by HCPs. This information includes the VAS for stress and pain and the Bluebelle Wound Healing Questionnaire, which includes pictures of the wound taken with the mobile app. The sampling frequency of these questionnaires was preset according to the advice of psychologists and surgeons.

## Methods

### Overview

The Adhera CARINAE Digital Health Program will be tested in a multicenter trial, including 5 clinical settings across 3 European countries, and will use a stratified randomized controlled design including 30 intervention participants (6 per clinical site) and 30 control group participants (6 per clinical site; Multimedia Appendix 5). This study aimed to obtain objective answers to the following 2 research questions:

Is the designed protocol feasible for conducting a future definitive randomized controlled trial? Accordingly, to what extent does the program affect patients’ and caregivers’ stress, anxiety, and pain levels, and secondarily, well-being and overall quality of life, compared with patients receiving the standard of care only?What is the overall usability of the digital health solution based on the experience of patients, caregivers, and HCP?

### Study Setting

After approval from the ethics board, the study will be conducted at the 5 departments of the following European hospitals:

Maastricht University Medical Center+ (UMC+; the Netherlands)—Cardiothoracic Surgery DepartmentHospital Universitario Reina Sofia (SAS; Spain)—Cardiothoracic Surgery DepartmentInstituto di Ricovero e Cura per Anziani (INRCA; Italy)—Urology DepartmentSant Joan de Déu Hospital (Spain)—Orthopaedics and Traumatology Department for ChildrenFundació Parc Taulí (Parc Taulí; Spain—Orthopaedics and Traumatology Department for Adults.

### Eligibility Criteria

#### Inclusion Criteria

The study included participants aged 8 to 65 years who underwent one of the following surgeries: cardiopulmonary bypass surgery (Maastricht UMC+); coronary artery bypass surgery (Maastricht UMC+); cardiac valve replacement (SAS, Maastricht UMC+); prostate, kidney, or bladder cancer surgery (INRCA); hip or knee replacement (HSJD; Parc Taulí); maxillofacial surgery (HSJD); orthognathic surgery (HSJD); or scoliosis (HSJD). Furthermore, adult study participants will have to have an Android smartphone and demonstrate basic digital literacy (eg, know how to communicate through instant messaging apps or similar). For children, their caregivers should have an Android smartphone and demonstrate basic digital literacy.

#### Exclusion Criteria

Potential participants who are unable to provide informed consent; communicate in the native language; demonstrate basic digital literacy; present symptoms of dementia; are allergic to dedicated wearable materials, such as steel and silicone; are pregnant; and are enrolled in another clinical trial will be excluded.

### Interventions

#### Overview

Eligible participants will be randomly assigned to the experimental group or the control group following block randomization of size 4 using the Sealed Envelope web-based tool [36]. The digital health solution includes 3 distinct components—that is, the mobile app, a VR component, and a clinical web application. The first and second components will be used by the participants in the experimental group, whereas the third will be used only by HCPs for those patients. Both the control and the experimental groups underwent the same visits. The trial was organized as shown in Figure 5.

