#### Randomization and Allocation

Participants-patients will be randomized through the prestratified randomization method to achieve balance between the 2 groups (intervention and control groups) according to the type of surgery and baseline characteristics (covariates). Stratified randomization was achieved by generating a separate block for each combination of covariates and participants were assigned to the appropriate block of covariates. The specific covariates in the clinical trial were represented by the type of surgery (3 surgeries) and sex (2 levels: male and female). With these 2 covariates, the possible block combinations totaled 6 (eg, male, cardiac valve replacement). According to this, the participants’ allocation will be blinded through an Excel file spreadsheet (RAND function) using permuted block randomization with a ratio of 1:1 between the intervention and control groups. Allocation concealment will be ensured, as we will not release the randomization code until the patients are recruited for the trial.

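### Two different randomisation procedures are described, and because site is a stratum in neither, the stated 6 per arm at each site is not guaranteed

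*Protocol article*

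**What the plan says.** Allocation is described in two places.

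- **Interventions, Overview:** assignment is made "following block randomization of size 4 using the Sealed Envelope web-based tool". No stratification factor is named.
- **Randomization and Allocation:** assignment is made "through an Excel file spreadsheet (RAND function) using permuted block randomization with a ratio of 1:1". It is stratified by "the type of surgery (3 surgeries) and sex (2 levels: male and female"), and "the possible block combinations totaled 6". No block size is given. The example of a stratum is men having a cardiac valve replacement.

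The Methods overview calls the design stratified and sets "30 intervention participants (6 per clinical site) and 30 control group participants (6 per clinical site"). The Inclusion Criteria list procedures by hospital, including "prostate, kidney, or bladder cancer surgery (INRCA); hip or knee replacement (HSJD; Parc Taulí); maxillofacial surgery (HSJD").

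Randomization and Allocation also says that the code is withheld until patients have been recruited. The Results section says that recruitment is complete and the primary impact analysis is under way.

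**The concern.** A web service and a spreadsheet random-number function are different sources for an allocation list. A reader cannot tell which one produced it, which strata applied, or how large the blocks were.

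The strata are also unclear in themselves, since three surgeries cannot be read off the procedure list. Neither account stratifies by site, so nothing in the described design secures the stated split at each site. The sites differ in country and surgical field, and one is a children's department. A lopsided split at a site therefore carries those differences into the arms by chance. In a trial of 60, that costs precision and makes the unadjusted result harder to read.

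**Working it through.** **1. The plan's own figures.** 5 sites x 6 = 30 per arm, 60 in all. 3 surgeries x 2 sexes = 6 strata. Both reproduce.

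**2. The two accounts side by side.**

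| | Interventions, Overview | Randomization and Allocation |
|---|---|---|
| Generator | Sealed Envelope web tool | Excel RAND |
| Block size | 4 | not given |
| Strata | none named | surgery (3) x sex (2) |
| Site as stratum | no | no |

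Block size and strata could be combined. The generators cannot both be the source of the list.

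**3. What the three surgeries are.** The Inclusion Criteria give eight entries: cardiopulmonary bypass, coronary bypass, valve replacement, urological cancer surgery, hip or knee replacement, maxillofacial, orthognathic and scoliosis surgery. If the levels are procedures, as the example suggests, most entries have no stratum. If they are the cardiac, traumatological and oncology use cases of the program overview, the example is wrong.

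On either reading, lists cross sites. Valve replacement is listed for both cardiac hospitals. Hip or knee replacement is listed for both the children's and the adult orthopaedic hospital.

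**4. Chance of 6:6 at each site.** Inputs from the article: 12 patients per site (6 + 6), blocks of 4, 1:1, strata of surgery x sex. Assumptions: the three levels are the use cases, mapped as cardiac = 2 sites, urology = 1 and orthopaedics (children's and adult) = 2; patients arrive in random order; the proportion of men, which the article does not give, is varied. There were 10,000 simulated trials per row.

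| Men: cardiac / urology / orthopaedic | All five sites 6:6 | At least one site 8:4 or worse | Total 30:30 |
|---|---|---|---|
| 50 / 50 / 50% | 2.3% | 51% | 36% |
| 70 / 85 / 50% | 2.6% | 52% | 37% |
| 70 / 100 / 50% | 3.9% | 50% | 46% |

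A cardiac or orthopaedic site reaches 6:6 about 30 to 31% of the time. The urology site does so about 62% of the time, or always if all its patients are men.

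Other list structures, for comparison:
- One unstratified list in blocks of 4: all five sites 6:6 in about 0.6%.
- Site x sex strata in blocks of 4: about 9 to 15%.
- Site alone in blocks of 4: 12 / 4 = 3 complete blocks, so 6:6 everywhere with certainty.

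**5. Predictability of blocks of 4.** Suppose the block size is known and every earlier allocation in the list is seen. There are 6 equally likely blocks.
- Certain in advance: the fourth place always, and the third when the first two match (probability 1/3). (1/3 + 1) / 4 = 1/3.
- Best guess correct, by place: 1/2, 2/3, 2/3, 1. The mean is (0.500 + 0.667 + 0.667 + 1.000) / 4 = 0.708.

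Now take a site that supplies half of a shared list and does not see the other site's enrolments. Best guessing is then right about 59% of the time, and in simulation essentially no assignment is certain.

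**The case against.** The two accounts can partly be fitted together. Twelve per site is three complete blocks of 4, so a separate web-tool list for each site would deliver exactly 6:6. But the article does not say that lists were kept by site, and on that reading the surgery x sex text would need correcting. The contradiction stands.

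The imbalance figures depend on a mapping of surgeries to sites that the article never makes. That is fair, and the mapping is labelled as an assumption. The conclusion was stable over the sex mixes tried, and one unstratified list does worse still.

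A reader might infer that site, country and age differences bias the comparison. They do not do so systematically: chance imbalance under 1:1 randomisation adds noise. The article also lists age, sex and surgery type as confounders, plans analyses split by surgery, and has a mixed model with surgery as a random factor and age or sex as possible covariates. This covers part of the problem, but site enters none of the models described.

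A reader might also infer that allocation was guessable. The article does not show that. The block size appears in a text that reports recruitment as already complete, the code is said to be withheld, and nothing says recruiters knew the size. Staff could see who received the programme, because they use the web application only for intervention patients, so the risk is real if the size was known. Even then, one third and 71% are upper bounds. They require sight of a whole list, whereas the imbalance figures assume lists shared between sites.

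**Conclusion.** The point holds in a limited form. The article names two generators that must be reconciled, its three surgery levels fit neither the eligibility list nor its own example, and the per-site split is stated without a mechanism that secures it. It would be too strong to say the strata cannot give 6:6, since they can by chance. Under the use-case mapping, with the sex mix varied, that happens at all five sites in about 2 to 4% of trials, and at least one site is 8:4 or worse in about half. Children and adults are likewise not balanced by design, because no stratum separates them.

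The predictability of blocks of 4 is a conditional remark, not a demonstrated flaw. The point should be acted on while analysis is still open, but it does not invalidate the randomisation.

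**What to change.** 1. Merge the two accounts into one that states the generator, block size and strata actually used, with the surgery levels defined by procedure or by group.
2. Replace the figure of 6 per arm per site with the numbers achieved in each arm at each site.
3. In the main model, enter site as a fixed effect with sex as a covariate, in place of the random surgery factor. Site also fixes the surgery group and separates the children's department.

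Changing the block scheme is no longer possible, as recruitment is complete. For a future trial, stratify by site: 12 per site in complete blocks gives exactly 6:6. Each site would then see its whole list, so the block size should be kept from recruiters.

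Cost: a text correction and 5 - 1 = 4 degrees of freedom for site. In a future trial stratified by site alone, sex would be balanced by adjustment rather than by design.

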**Figure 5 figure5:**
[figure not shown]
Flow of participants. GSE-SF: General Self-Efficacy Short Form; HADS: Hospital Anxiety and Depression Scale; NPS: Net Promoter Score; PAM-13: Patient Activation Measure short form; PANAS: Positive and Negative Affect Schedule; SUS: System Usability Scale; SWEMWBS: Short Warwick Edinburgh Mental Well-Being Scale; VAS: visual analogue scale.

#### Control Group

The control group will not use the digital solution and will receive standard care consisting of visits to the health care provider. Patients in the control group were provided with instructions on diet and healthy lifestyle habits; however, in current health care settings, it is not very common to provide patients with stress and anxiety perioperative relief support. Assessments of the control group will be performed during the following visits:

The initial visit on which the HCP communicates to the patient the need for surgery (2-4 weeks before surgery);Hospital admission (1-3 days before surgery);Hospital discharge (approximately 1 week after surgery);Remote follow-up 14 days after the surgery.

Following each visit, several questionnaires will be administered to patients with a duration ranging from 15 to 45 minutes according to the visit (Table 1).

**Table 1 table1:** Key parameters and measurements: baseline is 2-4 weeks before surgery, (hospital) admission is 1-3 days before surgery, (hospital) discharge is 1 week after surgery, and postoperative is 2 weeks after surgery.

Variables		Participants	Measurements	Baseline	Admission	Discharge	Postoperative
**Primary outcomes**							
	Self-reported stress	Patients and caregivers	VAS^a,stress^	Yes	Yes	Yes	Yes
	Self-reported pain	Patients	VAS^pain^	Yes	Yes	Yes	Yes
	Anxiety and depression	Patients	HADS^b^	Yes	Yes	Yes	Yes
**Secondary outcomes**							
	HRQoL^c^	Patients	EQ-5D-3L	Yes	Yes	Yes	No
	Emotional status	Patients	PANAS^d^	Yes	Yes	Yes	Yes
	Mental well-being	Patients and caregivers	SWEMWBS^e^	Yes	No	No	Yes
	Self-efficacy	Patients and caregivers	GSE-SF^f^	Yes	No	No	Yes
	Activation status	Patients	PAM-13^g^	Yes	Yes	No	Yes
**Usability outcomes**							
	CARINAE’s usability	Intervention group patients, HCPs^h^ and caregivers	SUS^i^	No	Yes	Yes	Yes
	Recommendation grade for CARINAE	Intervention group patients, HCPs and caregivers	NPS^j^	No	Yes	Yes	Yes
	General satisfaction with CARINAE	Intervention group patients, HCPs and caregivers	Ad hoc	No	Yes	Yes	Yes
**Covariates**							
	Demographics	Patients	Self-report assessment questionnaire	Yes	No	No	No
	Clinical data	HCPs	HCP report	Yes	Yes	Yes	Yes
	Length of hospital stay	Patients	HCP report	No	Yes	Yes	No

^a^VAS: visual analogue scale.

^b^HADS: Hospital Anxiety and Depression Scale.

^c^HRQoL: health-related quality of life.

^d^PANAS: Positive and Negative Affect Schedule.

^e^SWEMWBS: Short Warwick Edinburgh Mental Well-Being Scale.

^f^GSE-SF: General Self-Efficacy-Short Form.

^g^PAM-13: Patient Activation Measure short form.

^h^HCP: health care professional.

^i^SUS: Stem Usability Scale.

^j^NPS: Net Promoter Score.

#### Experimental (Intervention) Group

The experimental group will receive a digital health solution during the first visit, and training on how to use this tool will be provided. Patients will take the digital health solution home with them and can use it as often as they like. The experimental group, after each 1 of the 4 standard care visits, will complete the same questionnaires as the control group.

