### Outcome Variables

#### Research Question 1 (Primary and Secondary Outcome Variables)

Stress, anxiety, and pain represent the primary outcome variables that will be measured using paper-and-pencil questionnaires.

The secondary outcome variables were overall quality of life, emotional status, mental well-being, self-efficacy perception, and patient activation during and after hospital stay.

To assess the primary outcome variables, the following questionnaires will be used after each standard care visit and will be administered by paper and pencil:

Patients’ and caregivers’ *self-reported stress* was measured using a VAS at enrollment (baseline), at admission for surgery, at hospital discharge, and 2 weeks after surgery. Operationally, a VAS is usually a horizontal line, 100 mm in length, anchored by word descriptors at each end, such as no stress versus highest stress possible [37].Patients’ *self-reported pain* was measured using a VAS for pain measurement at enrollment (baseline), at admission for surgery, at hospital discharge, and 2 weeks after the surgery. The VAS for pain is a validated single-item scale that is anchored by “no pain” (score of 0) and “pain as bad as it could be” or “worst imaginable pain” (score of 100). The VAS presents a high internal consistency, as shown by a Cronbach α of 0.9117 [38].Patients’*Hospital Anxiety and Depression Scale* (HADS) scores were measured at admission for surgery, at hospital discharge, and 2 weeks after surgery. The HADS consists of 2 dimensions with 7 questions each, one representing the anxiety subscale and the other representing depression, with both psychopathological concepts of anxiety and depression being independent. Each item was rated on a 4-point frequency scale, ranging from 0 to 3. The internal consistency of the HADS, as measured by the Cronbach α coefficient, was found to be .78 for the anxiety subscale and .86 for the depression subscale, indicating satisfactory reliability [39].

To assess the secondary outcome variables, the following questionnaires will be used after each standard care visit and will be administered paper and pencil:

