### Data Analyses

The analyses will be conducted in Python 3.9.5 through the IDE PyCharm Community Edition 2021.2.1 Software and intention-to-treat principles. Descriptive statistics will be used to characterize the groups during the 4 visits. Furthermore, owing to the small sample size, Spearman correlations will be performed with all the variables to check, first, for potential associations between the variables and, second, differences between the intervention versus control groups. Further potential differences between these groups will be analyzed as follows:

Stress (VAS), pain (VAS), and mood state (PANAS-short form) will be subjected to a multivariate mixed analysis of variance (split-plot ANOVA) with “time” as a within-subject factor (ie, 4 time points) and “group” as a between-subject factor (intervention vs control).Patient activation (PAM-13) and self-efficacy (GSE-SF) will also be submitted to a multivariate mixed analysis of variance with “time” as a within-subject factor (Ie, 3 time points) and “group” as a between-subject factor (intervention vs control).Mental well-being (Short Warwick Edinburgh Mental Well-Being Scale) and HRQoL (EQ-5D-3L and EQ-5D-Y) will be analyzed using multivariate mixed analyses of covariance. As measurements of these 2 variables are based on a pre-post design, postmeasurements will be used as the dependent variable and premeasurements as covariates.

Finally, it is of interest to explore the effects as a function of different types of surgery. To this end, 2 different statistical approaches will be used:

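### As written, baseline questionnaires follow the first visit, during which one arm already receives the tool and training; the order is ambiguous and must be reconciled

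*Protocol article*

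**What the plan says.** - **Hand-over.** The Experimental (Intervention) Group section states the following: "The experimental group will receive a digital health solution during the first visit, and training on how to use this tool will be provided".
- **Questionnaires, intervention arm.** The same section says that these participants, "after each 1 of the 4 standard care visits, will complete the same questionnaires as the control group".
- **Questionnaires, control arm.** Under Control Group: "Following each visit, several questionnaires will be administered to patients".
- **Primary outcomes.** Under Research Question 1: "the following questionnaires will be used after each standard care visit and will be administered by paper and pencil". The secondary outcomes are introduced in the same way.
- **Baseline window.** The Control Group section puts the initial visit 2 to 4 weeks before surgery, and the caption of Table 1 gives the same window for baseline.
- **Competing label.** The individual outcome descriptions place the first measurement at enrolment. For stress, pain and emotional status they equate this with baseline.
- **Code release.** Under Randomization and Allocation: "we will not release the randomization code until the patients are recruited for the trial". The Recruitment section counts a patient as recruited once informed consent is given.
- **Use of baseline.** Under Data Analyses, stress, pain and mood enter a split-plot ANOVA with four time points. Patient activation and self-efficacy enter a similar model. For mental well-being and quality of life, "postmeasurements will be used as the dependent variable and premeasurements as covariates". A linear mixed model with time, group and their interaction is also planned for each variable.

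**The concern.** A baseline supports a between-arm comparison only if allocation cannot have influenced it. Here the outcomes are self-rated, and participants cannot be blinded to a tool that only one arm is handed. Learning one's arm, or being trained on a programme meant to relieve stress, could change a stress or mood rating at once.

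If baseline is rated after that moment, part of the effect (or of the reaction to allocation) sits in the baseline value. Contrasts of later visits with baseline then remove it from the estimate, covariate adjustment removes a fraction of it, and the baseline table no longer gives a clean check on randomization. The Limitations section names other sources of bias but not this one.

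**Working it through.** The protocol gives no figure on this point, so the check has two parts: the order of events, and an illustration of the consequence.

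**Order of events, taken literally**
1. Consent makes the patient recruited (Recruitment).
2. The code may be released from then on (Randomization and Allocation). This sets an earliest time only; release is not tied to completed baseline forms.
3. The tool is handed over, with training, during visit 1. Allocation must be known by then.
4. Questionnaires follow each visit, in both arms.
5. Baseline and visit 1 share one window, so the baseline forms are those that follow visit 1.

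Steps 3 to 5 put baseline after allocation and, in the intervention arm, after training. The enrolment label could point to an earlier moment, but the same section introduces those questionnaires as used after each visit. No passage puts them before allocation or hand-over.

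**Which analyses are affected**
- First time level: stress, pain, PANAS, PAM-13 and GSE-SF.
- Pre-measurement covariate: SWEMWBS and EQ-5D only.
- Anxiety (HADS) is left aside. Table 1 lists a baseline value, the outcome description omits it, and no outcome-specific analysis names it.

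**Size of the bias (all inputs are assumptions)**
Let τ be the true between-arm difference at follow-up, s the difference already present at baseline, and rho the correlation between baseline and follow-up, with equal SDs.
- Follow-up minus baseline estimates τ − s, so the bias is s.
- Covariance analysis estimates τ − rho × s, so the bias is rho × s.
- Contrasts among post-baseline visits do not involve s. The four-level time × group test mixes both kinds, so s does not carry over to it as a whole.

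| Assumed s (SD) | Baseline-referenced contrast | Covariance analysis, rho 0.3 | rho 0.5 | rho 0.7 |
|---|---|---|---|---|
| 0.1 | 0.10 | 0.03 | 0.05 | 0.07 |
| 0.2 | 0.20 | 0.06 | 0.10 | 0.14 |
| 0.3 | 0.30 | 0.09 | 0.15 | 0.21 |

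For scale, a plain comparison of 30 per arm (two-sided 0.05, power 0.8, normal approximation) detects (1.960 + 0.842) × √(2/30) = 0.723 SD. If τ were that large and s lay in the direction of benefit:
- the baseline-referenced estimate would keep (0.723 − 0.1)/0.723 = 86% of τ at s = 0.1 and (0.723 − 0.3)/0.723 = 59% at s = 0.3;
- the covariance estimate with rho 0.5 would keep (0.723 − 0.05)/0.723 = 93% and (0.723 − 0.15)/0.723 = 79%.

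**The case against.** The best defence is that the text does not settle the order. The enrolment label fits a measurement taken before release of the code. The allocation section says only that the code is not released before recruitment; a reader might infer that it is released at consent, but that is not stated. Table 1 collects no usability data at baseline, which fits a baseline meant to precede use. The tool is then taken home, so even on the worst reading the prior exposure is hand-over and training only. The participant flow figure and the SPIRIT table in Multimedia Appendix 5, which might show the order, are not available here. The study is also a feasibility trial.

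Most of this stands. It rules out the flat claim that baseline is a post-allocation measure. It does not remove the problem, because the literal sequence is stated in several places and nothing states the opposite. Blank usability cells at baseline fit equally well with a tool just handed over and not yet used enough to rate.

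Two further inferences would go too far. One is that the rho × s bias applies to stress: stress has no planned baseline covariate, so that formula belongs to SWEMWBS and EQ-5D. The other is that the bias runs towards no effect. Relief in one arm or disappointment in the other would act that way, but training that made the operation more vivid could raise baseline stress and act the other way.

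**Conclusion.** The point holds as a conflict or ambiguity in the stated order that bears on whether baseline is valid. Read literally, baseline stress, pain, mood, well-being, self-efficacy and activation are rated after allocation is known and, in one arm, after training. The documents do not establish that this happened in practice.

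The size and direction of any bias are unknown. The illustration, 0.1 to 0.3 SD for baseline-referenced contrasts and 0.05 to 0.15 SD for the covariance analyses at rho 0.5, rests on assumed shifts, an assumed correlation and equal SDs, none of which the protocol gives. It shows that the order is worth settling and does not estimate the actual bias.

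**What to change.** 1. **Text.** Reconcile the intervention, control and outcome sections, and state the visit 1 order: consent, all baseline questionnaires, release of allocation, then hand-over and training. This needs no added visit or form. As recruitment is complete, it cannot change this cohort, but it carries into the definitive trial that this study is meant to inform.
2. **Completed cohort.** Report, per participant or per site, whether baseline preceded allocation and hand-over.
3. **Sensitivity analysis.** Where it did not, or where the order is unknown, compare the arms at the post-baseline visits without the baseline value. Drop the baseline time level from the ANOVA and the mixed model and take the group effect over the remaining visits. For SWEMWBS and EQ-5D, drop the pre-measurement covariate.

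The cost is one flag, one extra analysis and some precision in that analysis. Without the covariate, the standard error grows by a factor of about 1/√(1 − rho²), which at an assumed rho of 0.5 is 1/√0.75 = 1.15.
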